**Figure 1 f1:**
[figure not shown]
A conceptual framework for the CarMeR Study.

This project, dubbed the Cardiometabolic Risks (CarMeR) Study, is by the Bill and Melinda Gates Foundation through the African Postdoctoral Initiative, managed by the African Academy of Sciences. The objectives are: 1. determine the prevalence of undiagnosed diabetes, prediabetes and other associated cardiovascular disease risks using the multi-sampled oral glucose tolerance test [OGTT] with 82.5g monohydrate dextrose, 2. characterize the phenotype of diabetes and prediabetes relative to body composition, body mass index (BMI), and other anthropometric measures, 3. establish the ocular characteristics and complications in people with diabetes and prediabetes, 4. ascertain whether the etiology of undiagnosed diabetes is predominantly insulin resistance or beta-cell insufficiency using homeostasis model analysis of beta [HOMA-β and HOMA-IR], 5. determine the sensitivity of diagnostic alternatives to the multi-sampled OGTT, specifically the fasting plasma glucose (FPG) test and the glycated hemoglobin (HbA1c) test, and 6. determine, over a 1-year period, if changes in food choices, physical activity, weight loss and psychosocial counseling influence reversal or prevention among people newly diagnosed with diabetes and prediabetes.

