### Biochemical measurements

#### Fasting blood collection and processing

Eligibility for participating in the OGTT requires participants to fast for at least eight hours, with permission to drink plenty of water from 8pm the night before sample collection. Medical Laboratory Scientists licensed by the Allied Health Profession Council of Ghana will collect the blood specimen using standard venipuncture techniques, with a vacuum blood collection system. Fasting blood specimen of 3ml is collected into one gel separator tube and 2ml each of fasting blood is collected into separate fluoride oxalate tubes for HbA1C and FPG analysis. The blood specimens are kept on ice and transported to the lab for processing and storage. An initial fasting blood glucose test is performed using an Accu-Chek Instant meter and Accu-Chek Instant test strip (Roche, Germany, 2019) to determine glucose tolerance levels and the safety of the participants before subsequent glucose administration for the OGTT procedure. Blood specimen for the other biochemical measurements in this study are also collected in the gel separator tube. These specimens are separated at 3000rpm for 3 minutes and the serum aliquoted into Eppendorf tubes for blood chemistry analysis, immunoassay analysis and storage for reference. For the specimen in the two fluoride oxalate tubes, one is separated and the plasma is aliquoted into Eppendorf tubes and used for fasting blood glucose analysis, whereas the other fluoride oxalate tube sample is used for HbA1c analysis.

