To assess the glucose metabolism of participants, an Oral Glucose Tolerance Test (OGTT) is performed as a gold standard diagnostic test. The OGTT assessment uses three time points where blood samples are collected at glucose time of 0, 60 and 120 minutes. The glucose 0’ blood specimen is taken and 82.5g of dextrose monohydrate (equivalent to 75g of anhydrous glucose) is dissolved in 250 ml of drinking water for the participants to drink within 3 minutes. While waiting for their blood to be collected, participants were monitored for any adverse reactions by a trained medical officer. After which blood specimens are taken twice more to assess OGTT glucose level values at 60 minutes and 120 minutes. Each of the time points will be used to diagnose glucose tolerance levels. Prior to the OGTT procedure, spot whole blood glucose analysis is performed to assess Fasting Blood Glucose (FBG). At baseline, blood specimen is also drawn to measure glycated hemoglobin (HbA1C) levels, inflammations (high-sensitivity C-reactive protein [hsCRP], interleukin 6 [IL6]), lipid panels (serum cholesterol, plasma HDL, LDL, TG) and cortisol (a measure of physiologic stress). Specimens for creatinine, liver function tests (AST and ALT), and total protein levels are also taken to measure kidney and renal function. For the OGTT procedure, 10ml of blood is sampled at each time point from each participant, totaling 30ml per participant.

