#### Diagnoses

Diagnosis of abnormal glucose tolerance in the CarMeR study will be done using fasting plasma glucose (FPG), HbA1c and OGTT diagnostic tests based on the criteria suggested by the International Experts Committee Report on Diabetes and American Diabetes Association (59, 60). Participants are classified as having prediabetes if they have an FPG level between 5.6mmol/L and 6.9 mmol/L (100mg/dl and 125mg/dl), or an HbA1c level between 5.7% and 6.4% or a 2-hour OGTT result between 140mg/dl and 199mg/dl. Participants are classified as having diabetes if they have an FPG level of 7.0 mmol/L or higher (126mg/dl or higher), or HbA1c level of 6.5% or higher, or a 2-hour OGTT result of 200mg/dl or higher. Additionally, 1-hour post load plasma glucose (PG) will be used to diagnosed hyperglycemia (IH) and diabetes. Participant with a 1-h PG ≥ 155 mg/dL (8.6 mmol/L) are considered to have IH and should be prescribed lifestyle interventions and referred to a diabetes prevention program. Participants with a 1-h PG ≥ 209 mg/dL (11.6 mmol/L) will be considered to have diabetes. Generalized obesity is defined as body mass index (BMI) ≥30 kg/m^2^, and central obesity as a waist circumstance >102 cm in men or >88 cm in women, and a waist-to-hip (WHR of 0.88-0.89 (61, 62). Certified medical laboratory diagnostic scientists will perform all blood sample analysis at the Cardiometabolic Epidemiology Research Laboratory (CERL).

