### Data analysis

For the accuracy of data and information, data collected through the Kobo Collect toolbox application will be downloaded into an Excel spreadsheet and screened visually and statistically. Data will be analyzed and interpreted by the principal investigator and his local collaborators and shared back with foreign collaborators. In the attempt to make the findings of the study public, data analysis will be conducted using STATA 16 and SPSS 23. Statistical tools specific and relevant to the research questions and hypotheses of the CarMeR study would be used. To determine the prevalence of undiagnosed diabetes, prediabetes and other associated cardiovascular risks, data on OGTT, FPG and HbA1c will be analyzed using descriptive statistics (percentages and confidence intervals). In order to investigate the differences in phenotype, diabetes, prediabetes, and normoglycemic groups will be compared based on BMI and body composition (waist hip ratio, body fat percentage, skeletal muscle, total body water) using analysis of variance (ANOVA) and t-test. To profile the ocular characteristics and complications of the diabetes and prediabetes groups, a cross-tabulation and a subsequent chi-square test will be done to assess the association between glycemic dysregulation and the presence of ocular complications (diabetic retinopathy, cataract, macular edema). For the purpose of ascertaining whether the predominant etiological factor of undiagnosed diabetes in this populations is insulin resistance or beta-cell failure, a homeostasis model analysis of beta [HOMA-β and HOMA-IR] will be computed and logistic regression will be used to determine the dominant factor. As a way of determining the sensitivity of other diagnostic alternatives (FPG and HbA1c) in comparison to the multi-sampled OGTT, receiver-operated characteristics (ROC curves), including sensitivity and specificity curves, will be used. Finally, to ascertain whether lifestyle changes (food choice, physical activity, weight loss, psychosocial counseling) over a one-year period impacts biomarkers of glucose regulation, a linear mixed model regression analysis, controlled for baseline characteristics will be used. T-tests will be conducted to observe changes in glucose regulation biomarkers.

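### The OGTT reference for judging FPG and HbA1c is not clearly fixed, and if its 0-minute fasting sample counts, FPG is partly compared with itself

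*Protocol article*

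**What the plan says.** Objective 5, in the list that closes the Introduction, is to "determine the sensitivity of diagnostic alternatives to the multi-sampled OGTT, specifically the fasting plasma glucose (FPG) test" and the HbA1c test. The Data analysis section repeats this as "determining the sensitivity of other diagnostic alternatives (FPG and HbA1c) in comparison to the multi-sampled OGTT", using ROC curves with sensitivity and specificity.

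The section on fasting blood collection and processing describes the OGTT: "The OGTT assessment uses three time points where blood samples are collected at glucose time of 0, 60 and 120 minutes". It adds: "Each of the time points will be used to diagnose glucose tolerance levels".

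The Diagnoses section treats FPG, HbA1c and OGTT as three tests. Its diabetes criteria include:
- FPG: "Participants are classified as having diabetes if they have an FPG level of 7.0 mmol/L or higher"
- OGTT: "or a 2-hour OGTT result of 200mg/dl or higher"
- 1-hour value: "Participants with a 1-h PG ≥ 209 mg/dL (11.6 mmol/L) will be considered to have diabetes"

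On specimens, "2ml each of fasting blood is collected into separate fluoride oxalate tubes for HbA1C and FPG analysis". The same section also describes a 0-minute specimen taken before the glucose drink. The article does not say whether the FPG tube and the 0-minute specimen yield one assay result. Nor does it say how the three time points combine into a single reference result for objective 5.

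**The concern.** The 0-minute sample of an OGTT is a fasting glucose, and the only plasma limits the article gives for a fasting sample are its FPG limits. On the specimen section's wording, the fasting value therefore belongs to the reference against which FPG is judged. This is incorporation bias: a person positive on FPG alone stops being a false positive and becomes a true positive. HbA1c gets no such help, so the comparison between the two alternatives is uneven.

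Objective 5 asks whether a simpler test can stand in for the OGTT. What matters there is how many people only post-load glucose would find, and a reference that includes the fasting value understates that share for FPG. The choice of reference could also decide which test looks better, so it should be settled before the data are seen.

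**Working it through.** The article states no sensitivity, specificity, AUC or sample size for objective 5, so there is no planned figure to reproduce.

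**Step 1: algebra.** Cross-classify participants by FPG and by a post-load reference (1-hour or 2-hour positive):
- a = FPG positive, post-load positive
- b = FPG positive, post-load negative
- c = FPG negative, post-load positive
- d = both negative

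Post-load reference: sensitivity = a/(a+c), specificity = d/(b+d).

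Any of the three time points, with the 0-minute value identical to FPG: sensitivity = (a+b)/(a+b+c), specificity = d/d = 100%.

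The second sensitivity can never be below the first, because b is added to both numerator and denominator.

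**Step 2: illustration on 1200 people.** Assumed counts are a = 24, b = 12, c = 36, d = 1128.
- Post-load reference: sensitivity 24/60 = 40.0%, specificity 1128/1140 = 98.9%.
- Any time point: sensitivity 36/72 = 50.0%, specificity 1128/1128 = 100%.

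**Step 3: size over a range.** All inputs are assumed: 2-hour-positive 6.5%, 1-hour-positive 7.5%, 1-hour/2-hour correlation 0.8, multivariate-normal latent values, identical fasting results. Sensitivity comes from the normal probabilities and AUC from simulation. Each arrow runs from the 1-hour/2-hour reference to the same reference plus the 0-minute value.

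| FPG-positive | Fasting/post-load correlation | Sensitivity | AUC |
|---|---|---|---|
| 3% | 0.4 | 10.5% → 24.5% | 0.72 → 0.78 |
| 3% | 0.6 | 16.5% → 25.8% | 0.83 → 0.86 |
| 3% | 0.75 | 22.1% → 27.2% | 0.91 → 0.92 |
| 4% | 0.4 | 13.2% → 30.9% | 0.72 → 0.80 |
| 4% | 0.6 | 20.6% → 32.8% | 0.83 → 0.87 |
| 4% | 0.75 | 27.8% → 34.9% | 0.91 → 0.92 |

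The sensitivity gain runs from 27.2 − 22.1 = about 5 points to 30.9 − 13.2 = about 18 points. The AUC gain is about 0.01 to 0.07.

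**Step 4: dependence on the inputs.** A second assumed set (FPG-positive 3% or 5%, 2-hour-positive 5%, 1-hour-positive 6%, correlation 0.3-0.7) gives sensitivity of 8.6-33.0% against 1-hour/2-hour and 28.5-47.4% with the 0-minute value added, with AUC gains of about 0.02-0.12. The direction is the same and the size differs.

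**Step 5: limits of the 100% figure.** Under the second set:
- If FPG and the 0-minute value are separate assays and FPG carries a 3% CV, specificity at 7.0 mmol/L is 99.3-99.7%.
- If FPG is read at 5.6 mmol/L against a diabetes reference that includes the 0-minute value and both post-load values, specificity is about 76-80%.

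**The case against.** The strongest reply is that the article can be read without any incorporation. The Diagnoses section names FPG and OGTT as distinct tests and attaches the OGTT criterion to the 2-hour result, with a 1-hour criterion besides. Objective 5 calls FPG an alternative to the OGTT, and entry to the lifestyle intervention uses only the 2-hour value. On that reading the reference is already post-load, and its coding is detail a condensed article may leave to a fuller document.

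Much of this stands, and the point has to be conditional. But the article does not simply leave the reference open. It names a multi-sampled test and says that each sample, the fasting one included, is diagnostic. The two sections support different references that give different answers.

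A reader might infer three stronger claims that the documents do not support:
- **FPG specificity is certain to be 100%.** This needs an any-positive rule, a shared fasting result, and an index cut-off at or above the reference cut-off. The first two are not stated, and the third fails along much of a ROC curve.
- **The inflation is about 21 points.** With 2-hour-positive 6.5%, FPG-positive 4% and correlation 0.6, FPG sensitivity goes from 24% against 2-hour glucose alone to 45% against 0-or-2-hour (AUC 0.84 to 0.90). That second reference omits the 1-hour sample, so it is not the three-point OGTT. With the 1-hour value in both references the change is 21% to 33%.
- **HbA1c is built into the reference as well.** That would be so only if the any-test classification in Diagnoses served as the reference, and Data analysis names the OGTT instead.

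**Conclusion.** The concern holds in conditional form. The article leaves two readings of the objective 5 reference, and one of them makes FPG part of its own reference. Under that reading, with an any-positive rule:
- specificity at the matching cut-off is 100% if the fasting result is shared, and close to it if the assays are separate;
- sensitivity cannot be lower than against the same post-load reference when the fasting result is shared, and on the first set of assumed inputs it is about 5-18 points higher;
- AUC was higher in every scenario run, by about 0.01-0.07 on those inputs.

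The direction for sensitivity and specificity follows from the algebra. The direction for AUC and all the sizes rest on assumed inputs.

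Objective 5 is one of six, and the prevalence, phenotype and intervention results do not depend on it. All three glucose values are collected under either reading, so no data are lost. This should be fixed before analysis, as a cheap improvement; it does not threaten the study's main purpose.

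**What to change.** Add one sentence to Data analysis: for objective 5 the reference standard is post-load glucose only, with the 2-hour value as primary reference and the 1-hour value (or 1-hour/2-hour combined) as secondary, excluding the 0-minute value and HbA1c. State there that FPG and HbA1c are compared on the same participants with paired methods for AUC and sensitivity. Align the specimen section's statement about diagnostic time points with this definition.

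No new samples or visits are needed. The cost is the sentence itself and FPG accuracy figures that will look less favourable than under a reference containing the fasting value.

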**Methods and analysis:**

The study employs a community-based quasi-experimental design, making use of pre- and post-intervention data, as well as a questionnaire survey of 1200 individuals residing in the Cape Coast metropolis to ascertain the prevalence and risk factors for undiagnosed diabetes and prediabetes. Physical activity, dietary habits, stress levels, sleep patterns, body image perception, and demographic characteristics will be assessed. Glucose dysregulation will be detected using oral glucose tolerance test, fasting plasma glucose, and glycated hemoglobin. Liver and kidney function will also be assessed. Diabetes and prediabetes will be classified using the American Diabetes Association criteria. Descriptive statistics, including percentages, will be used to determine the prevalence of undiagnosed diabetes and cardiovascular risks. Inferential statistics, including ANOVA, t-tests, chi-square tests, ROC curves, logistic regression, and linear mixed model regression will be used to analyze the phenotypic variations in the population, ocular characteristics, glycemic levels, sensitivity levels of diagnostic tests, etiological cause of diabetes in the population, and effects of lifestyle modifications, respectively. Additionally, t-tests will be used to assess changes in glucose regulation biomarkers after lifestyle modifications.

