Non-African studies have shown the possibility of diabetes and prediabetes remission through non-pharmacological interventions (31, 32), making it important to replicate and improve on these studies in a typical African-born population. Although some studies from developed countries have shown lifestyle changes to significantly influence diabetes remission (33–36), no prospective study done in sub-Saharan Africa and Ghana has shown the possibility of people newly diagnosed with diabetes reverting to prediabetes or people with prediabetes reverting to normal glucose tolerance through non-pharmacological lifestyle interventions. These reasons, as well as the high prevalence of undiagnosed diabetes and the projected increase of 143% by 2045, have necessitated the inception and execution of this project. This project assesses the role of lifestyle choices, environmental exposures, psychosocial factors and nutrition on the prevalence of obesity, hypertension and diabetes (CMD risk factors) among Ghanaians, and how these contribute to improved health and visual outcomes.

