## Methods

The CarMeR Study will be executed by a multidisciplinary team of researchers from the University of Cape Coast, its Directorate of Health Services, the Rwanda National Hospital, and the University of Global Health Equity, Rwanda. To obtain reliable and valid results, the CarMeR Study will adhere to gold standards in all aspects of the project, including but not limited to the selection of communities, standardization of study protocols, adherence to ethical principles in the sampling procedures, anthropometric measurements, blood glucose testing, chemistry measurements, eye examination, blood pressure measurements, and surveys. The CarMeR Study will adopt the WHO-STEPwise approach for assessing cardiometabolic risk factors The STEPwise approach to surveillance (STEPS) is an NCD surveillance tool recommended by the WHO since 2005 for monitoring trends across countries (38, 39). The WHO-STEPwise instrument comprises three distinct phases or “steps” for evaluating risk factors. The first step is a questionnaire-based assessment, the second step comprises of physical measures and the third step comprises of biochemical measures (40). This instrument is a simplified and standardized approach to surveillance for collecting, analyzing and disseminating data on key risk factors especially for NCDs (38). In addition to a questionnaire survey, a community-based quasi-experimental design will be utilized to assess the glucose tolerance of all participants after administration of 82.5g monohydrate dextrose, in order to ascertain the prevalence and risk factors for undiagnosed diabetes and prediabetes. Subsequently, all consenting participants diagnosed with abnormal glucose tolerance will be enrolled into a community-based randomized controlled trial (RCT) to measure the effectiveness of lifestyle interventions on diabetes remission.

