#### Inclusion criteria

Participants would be included in the study if they aged 25 to 70 years, and have not been diagnosed with prediabetes or diabetes. Additionally, participants should be willing to undergo the screening procedure (glucose testing, eye examination, BMI assessment, lipid level measurement, and body composition analysis). Participants diagnosed of diabetes based on a 2-hour OGTT glucose level between 11.1-17.0mml/L (200-300mg/dL) or prediabetes with 2-hour OGTT glucose level between 7.8-11.0 mmol/L (140-199mg/dL), would be followed up with a non-pharmacological lifestyle intervention for one year to assess the effect on their glucose tolerance.

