### Expected outcomes

The CarMeR study is expected to help provide insights on the burden and possible management of diabetes, prediabetes and related cardiometabolic complications in a typical African population. It will ascertain the prevalence of undiagnosed diabetes and prediabetes, as well as explore the relationship between these diseases and cardiovascular risks such as obesity, dietary habits, socioeconomic status, stress, sleep pattern and location. Furthermore, it will provide a nuanced understanding of the phenotypic and biochemical characteristics of the people with diabetes and prediabetes, with a focus on body composition, insulin resistance, and beta-cell function. The study will also describe the ocular characteristics of the participants, in order to identify the ocular complications associated with abnormal glucose tolerance. In the subsequent phase of the study, the efficacy of lifestyle interventions like diet, physical activity, and psychosocial counseling in preventing or reversing diabetes and prediabetes, will be assessed.

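### The one-year question is reversal, prevention or remission, but the only analyses named for it are of mean changes in glucose biomarkers; no analysis of category change is planned

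*Protocol article*

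**What the plan says.** Three places in the protocol article frame the one-year question as a change of state:

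- The sixth objective (end of the Introduction, after Figure 1) asks whether changes in diet, activity, weight and counseling "influence reversal or prevention among people newly diagnosed with diabetes and prediabetes".
- The opening of Methods describes a randomized controlled trial "to measure the effectiveness of lifestyle interventions on diabetes remission".
- Expected outcomes says that the efficacy of lifestyle interventions "in preventing or reversing diabetes and prediabetes, will be assessed".

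The Data analysis section goes through the objectives in turn. For this one it asks whether lifestyle changes "over a one-year period impacts biomarkers of glucose regulation, a linear mixed model regression analysis, controlled for baseline characteristics will be used". It then adds: "T-tests will be conducted to observe changes in glucose regulation biomarkers". The Abstract matches: "t-tests will be used to assess changes in glucose regulation biomarkers after lifestyle modifications".

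Inclusion criteria says that participants with abnormal 2-hour values "would be followed up with a non-pharmacological lifestyle intervention for one year to assess the effect on their glucose tolerance". The Diagnoses section gives the cut-offs for prediabetes and diabetes on each test.

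**The concern.** Reversal, remission and prevention describe whether a person crosses a diagnostic boundary. A linear mixed model and t-tests on biomarkers describe how far an average moves. These are different quantities. An average can fall while few people cross a boundary, and people just above a boundary can cross it with almost no movement in the average.

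If the analysis is carried out as written, the study can report a mean change in HbA1c or glucose. It has no planned result for the proportion who reverted, stayed or progressed, which is what the sixth objective asks.

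**Working it through.** No figure of the plan is at issue, so there is none to reproduce. The check sets the text side by side and then illustrates why the two quantities differ.

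**1. Is a category analysis planned anywhere?** In Data analysis, the only logistic regression serves the etiology objective (HOMA-β against HOMA-IR), and the only chi-square test serves ocular complications. Percentages with confidence intervals serve baseline prevalence. For the one-year objective only the mixed model and t-tests remain. No section plans a one-year proportion or a table of transitions.

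**2. Does a mean change fix the reversal proportion?** The documents give no distribution, so these inputs are assumptions: baseline 2-hour glucose uniform on 200–299 mg/dL, random noise with SD 10 mg/dL at one year, and reversal meaning a value below 200 mg/dL. Each row holds the mean fall constant and varies only who improves. In the last two columns a quarter of participants fall by four times the mean and the rest do not change.

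| Mean fall (mg/dL) | Everyone falls equally | A random quarter falls | The highest quarter falls |
|---|---|---|---|
| 10 | 11.0% | 13.1% | 4.0% |
| 20 | 20.3% | 23.2% | 11.4% |
| 30 | 30.3% | 27.9% | 28.9% |

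A fall of 10 mg/dL goes with 4% to 13% reverted, and a fall of 20 mg/dL with 11% to 23%. At 30 mg/dL the three patterns nearly agree (28% to 30%), so the size of the gap depends on the scenario.

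**3. Would an uncontrolled count of reversals be enough?** No. Under the same assumptions, noise alone takes some people below 200 mg/dL. With no true change the share is SD × φ(0) / width = 10 × 0.399 / 99 = 0.040, or 4%. This accounts for the whole 4.0% in the first row, last column: that quarter starts above about 274 mg/dL and falls by 40, so it stays well above 200. Because participants are selected for a high value, part of any apparent reversal is regression to the mean. Only a comparison between arms removes it.

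**4. Which test would define the category?** The passages on entry do not agree:

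- Methods enrols every consenting participant found to have abnormal glucose tolerance.
- Diagnoses classifies on FPG, HbA1c or 2-hour glucose, and additionally on 1-hour glucose. It links a raised 1-hour value to lifestyle intervention.
- Inclusion criteria uses 2-hour bands for diabetes and prediabetes.
- Enrollment visit names only the diabetes band for the follow-up cohort.

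The choice matters. A hypothetical participant who enters with a 2-hour value of 11.5 mmol/L and ends with 7.5 mmol/L and HbA1c 6.6% is normal on the 2-hour test and diabetic on the any-test rule. Conversely, someone enrolled on HbA1c or FPG with a normal 2-hour value cannot move down on the 2-hour test. The bands in Inclusion criteria (7.8–11.0 and 11.1–17.0 mmol/L) cannot serve as the outcome scale, since they have no normal band and none above 17.0. The cut-offs in Diagnoses cover the full range.

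**5. How many participants?** Participants gives 1200 recruits and 6–7% undiagnosed diabetes: 1200 × 0.06 = 72 and 1200 × 0.07 = 84. This is an upper limit at that prevalence, before consent, referral of those at or above 17.0 mmol/L, and attrition. One person is 1/84 = 1.2 to 1/72 = 1.4 percentage points. If these were split equally into 36–42 per arm (an assumption; no ratio is given), the 95% half-width for a difference in proportions is 1.96 × √(2p(1−p)/n). With p = 0.11 and n = 42 it is 0.13; with p = 0.30 and n = 36 it is 0.21.

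**The case against.** The strongest reply is that this is a condensed article. The exact definition of remission, and the test that counts, are commonly left to the full protocol or analysis plan. A continuous outcome is also a defensible and more efficient choice when the group is small. Much of this stands: the absence of a detailed remission definition is not in itself a fault here, and the mixed model is a reasonable analysis to keep. It does not remove the point, because the article does not leave the analysis open. It names one for this objective, and that analysis has a different target.

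Several stronger readings are tempting, and the documents do not support them:

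- **That the study never measures reversal.** Inclusion criteria implies that glucose tolerance is assessed at one year, so category change could be derived. What is missing is a planned analysis of it.
- **That the Introduction adopts a definition of reversal.** Its phrase about people "newly diagnosed with diabetes reverting to prediabetes or people with prediabetes reverting to normal glucose tolerance" describes a gap in earlier research in the region.
- **That entry is by 2-hour glucose alone.** Inclusion criteria reads that way, but Methods taken with Diagnoses does not.
- **That any remission claim would be chosen after seeing the data.** This cannot be known without the full protocol and analysis plan.
- **That drug-treated participants would be counted as lifestyle reversals.** No section describes glucose-lowering drugs in the lifestyle cohort. The only mention of medical treatment there is referral of those with the highest 2-hour values.
- **That the choice of definition would shift the reversal rate by a stated amount.** The documents give nothing on how often the tests disagree, so no figure can be put on it.

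**Conclusion.** The mismatch holds on the article's own wording: the one-year question is a change of glucose category, and the only analyses named are of biomarker means. The conclusion rests on the text and on no calculation. The illustration shows that the difference can matter (4% to 13% reverted for one and the same mean fall), but its inputs are assumed and it is not an estimate for this study.

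This should be fixed before the one-year data are analysed. It is not more serious than that. Exclusion criteria and the Abstract's Purpose put the prevalence of undiagnosed diabetes first, reversal is the last of six objectives, and the data needed appear to be intended.

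**What to change.** In Data analysis, for the sixth objective:

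1. Add a 12-month outcome of glucose category (normal, prediabetes, diabetes), using the cut-offs in Diagnoses on one named test, such as the 2-hour OGTT. State the any-test classification as a sensitivity definition.
2. Compare the proportions who moved down, stayed or moved up between the randomized arms, for example with a risk difference or a logistic model adjusted for baseline glucose. Do this separately for those entering with diabetes and with prediabetes. On three categories, those entering with diabetes can only stay or move down; progression applies to the prediabetes group.
3. Keep the mixed model on biomarkers alongside.
4. Reconcile the descriptions of entry in Methods, Inclusion criteria, Diagnoses and Enrollment visit, so that the entry test and the outcome test match.

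Step 2 relies on the statement in Methods that this phase is a randomized controlled trial.

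The cost is mostly wording, given that glucose tolerance is to be assessed at one year. The real downside is precision. With at most 72 to 84 people entering with diabetes, the comparison in that group would be wide (a half-width of roughly 13 to 21 percentage points under the assumptions above). That is a good reason to report the mixed model next to it.
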